Moreover, a longer-term evaluation will take place for both groups but only for the primary outcome variables, as the interview entailing both primary and secondary outcomes is long and by extending the evaluation time frame, we would not want to lose participants at longer follow-ups and risk the emergence of attrition bias.

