### Sample size

Based on the power analysis (power=0.90), we estimated that the sample size of our study should be 212 participants (106 people per group) to detect differences between the two clinical groups. The power calculation was based on a moderate effect size (Cohen’ s d= 0.45) due to the naturalistic character of the study. A recent meta-analysis (58) established this value of Cohen’s d, calculating the effect size for borderline symptom trials as either 0.31 or 0.56, depending on the stand-alone or add-on design. Accessing these data, the authors decided to set the effect size as 0.45, which is a moderate value that is neither strict nor lenient. Before we reach the aforementioned sample size, we start processing our data within subjects, where a smaller sample size of 158 participants (79 per group) is needed to obtain a significant power of 0.80. The software used to calculate the power was R version 4.0.3.

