### Statistical analyses

#### Assessing the comparability of the two groups

Prior to the initiation of treatment, i.e., at baseline, the two groups will be compared for potential differences in all primary and secondary outcome variables: severity of BPD symptoms, self – harm and suicidality, severity of psychopathological symptoms, quality of life, quality and intensity of interpersonal relationships, functioning and disability. Due to being many outcome variables, MANOVA will be employed. Moreover, the two groups will be compared for potential differences in various socio-demographic variables as well as the presence of physical illness and details of the medication regime for BPD, by employing t-tests for independent samples. In line with this, socio-demographic and other variables that are significantly different between the two groups will be considered to be confounder variables and will be inserted as such in all ensuing analyses.

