#### Evaluation of effect

For evaluating the effect of the group assignment (intervention *vs* control) on the primary and secondary outcome variables, multiple linear regression models will be computed for each outcome variables. As predictors the following variables will be inserted: the baseline measurement of the outcome variable of interest, treatment duration, number of sessions attended and all variables that emerged as confounders at baseline (i.e. socio-demographic and other variables that were significantly different across groups).

This analysis will be replicated for all evaluation time points: T_1_ – T_4_. For time points T_6_-T_10_, it will occur only for the two primary outcome variables.

At the end of the study, a Repeated Measures ANOVA with the group assignment (IV) and the 11 time points of assessment (baseline, T_1_ – T_10_) will be performed for the two primary outcome variables.

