#### Dropout rates

Dropout rates will be compared at the end of the study with the non-parametric criterion Mann Whitney (IV: group assignment and DV: number of drop outs), as number of drop-outs is an ordinal variable.

The Statistical Package for the Social Sciences (SPSS) version 25 (95) will be used for the statistical analyses. All significance tests will be two-tailed, with a 5% significance level and 95% confidence interval.

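### The end-of-study Repeated Measures ANOVA keeps only patients seen at all 11 assessments over 5 years; the regressions skip T5, and the dropout variable is misdescribed

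*Protocol article*

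**What the plan says.** **End-of-study analysis.** The Evaluation of effect section of the protocol article plans "a Repeated Measures ANOVA with the group assignment (IV) and the 11 time points of assessment" (baseline and T1 to T10) for the two primary outcomes. The software is SPSS version 25. The sentence names no covariates.

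**Visit-wise analyses.** The same section plans a multiple linear regression for each outcome at T1 to T4. The predictors are the baseline value, treatment duration, number of sessions and the baseline confounders. For T6 to T10, "it will occur only for the two primary outcome variables". T5 is not mentioned, although the Design section and Table 1 schedule both primary outcomes at T5 (2 years and 6 months).

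**Adjustment rules.** Under Assessing the comparability of the two groups, variables that differ between the groups "will be considered to be confounder variables and will be inserted as such in all ensuing analyses". The Design section treats baseline outcome values as confounders of the later measurements. Limitations and challenges repeats that baseline differences are adjusted for at T1 to T10.

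**Missing data.** Aims and hypotheses gives the reason for restricting the longer follow-up to primary outcomes: "we would not want to lose participants at longer follow-ups and risk the emergence of attrition bias". For clinical outcomes no handling of missing values is stated. The one sentence on missing values (no imputation of intermittent gaps) and the one mention of intention-to-treat both belong to the economic evaluation.

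**Dropout.** "Dropout rates will be compared at the end of the study with the non-parametric criterion Mann Whitney", on the ground that the number of drop-outs is ordinal.

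**The concern.** A classical Repeated Measures ANOVA needs a complete row per patient. One missed visit out of ten follow-ups removes the patient, including all values that were observed. The article recognises attrition as a threat and then chooses, for its one joint analysis of all visits, a method that is very sensitive to it.

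Two things are at stake. The first is precision, because the completer set may be much smaller than 212. The second is selection. The arms differ in intensity: mainly group therapy once or twice weekly for 3 years in one, a 30-minute monthly session in the other. Those who complete every visit may therefore be selected differently in each arm, on top of non-random allocation.

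Three smaller faults sit beside this. The ANOVA uses baseline as one of its outcome levels, whereas the Design section treats it as a confounder. The regressions leave out a scheduled visit. The dropout comparison is built on a variable that is not what the text says it is.

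**Working it through.** **1. The plan's own sample size.** Inputs: "the authors decided to set the effect size as 0.45", power 0.90, two-sided 5% (Sample size; Dropout rates). The normal approximation gives n per group = 2 × (1.960 + 1.282)² / 0.45² = 103.8, so 104. The two-sample t-test gives 104.7, so 105. With the stated 106 per group, t-test power is 0.903. The figure of 212 therefore reproduces. It is explained by effect size, alpha and power alone, with no visible allowance for missing data. The second figure (158 at power 0.80) also reproduces, at 79 per group by t-test.

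**2. Complete cases.** The documents give no miss rate, so the rates here are assumptions. If each of the 10 follow-up visits is missed independently with probability q, the share with all values is (1 − q)^10. The same formula holds if q is the share of those still in follow-up who leave for good before each visit. Power is that of a two-group t-test at d = 0.45 with 106 × (1 − q)^10 per group. It is a yardstick for lost information, not the power of the ANOVA.

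| q per visit | Complete | Of 212 | Yardstick power |
|---|---|---|---|
| 0 | 100% | 212 | 0.90 |
| 1% | 90% | 192 | 0.87 |
| 3% | 74% | 156 | 0.80 |
| 5% | 60% | 127 | 0.71 |
| 10% | 35% | 74 | 0.48 |

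**3. Sensitivity to clustering.** Missed visits tend to fall on the same patients. At the extreme, if the same 10% of patients account for every miss, 90% are complete: 191 of 212, yardstick power 0.87 instead of 0.48. In terms of patients with at least one missed visit, 20%, 30% or 50% leaves about 170, 148 or 106, with yardstick power 0.83, 0.78 or 0.63.

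**4. Why the yardstick is not the ANOVA's power.** Assume compound symmetry with correlation ρ, d = 0.45 at all ten follow-ups and zero at baseline. The group effect on the 11-visit mean is 0.45 × 10/11 = 0.409, with variance (1 + 10ρ)/11. With 63.5 completers per group (q = 5%), the standardised effect is 0.409 / √((1 + 10ρ)/11), and the noncentrality is that value × √(63.5/2).

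- ρ = 0.5: 0.554, noncentrality 3.12, power about 0.87
- ρ = 0.7: 0.480, noncentrality 2.70, power about 0.77
- ρ = 0.8: 0.452, noncentrality 2.55, power about 0.72

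The yardstick of 0.71 is thus near the pessimistic end for the group effect. The group-by-time test was not calculated.

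**5. T5.** The Design section and Table 1 schedule it, Limitations and challenges promises adjustment at T1 to T10, and the ANOVA includes it. The regressions go from T4 to T6.

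**6. Dropout.** If the variable is the number of drop-outs per arm, there is one value against one, and the exact Mann-Whitney p is always 1.0. If dropout is coded 0/1 per patient, Mann-Whitney and chi-square nearly coincide. For illustrative counts of 20/106 against 35/106 they give p = 0.0190 and 0.0188; for 30/106 against 45/106, 0.0316 and 0.0312.

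**The case against.** The strongest defence is that the ANOVA is not the only analysis of effect. The visit-wise regressions come first in the section, adjust for baseline and confounders, and each needs only baseline, its covariates and that visit. This stands. A reader might infer that the long-term conclusion rests wholly on completers; the documents do not support that. The ANOVA nevertheless remains the only planned analysis of the primary outcomes that joins all visits.

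A reader might also infer that the ANOVA omits the confounders. Its sentence is silent, but the general rule covers all later analyses and Limitations and challenges extends it to T1 to T10. What remains is a need to reconcile the passages. Including baseline as an occasion and testing group by time is an accepted parameterisation in itself; the difficulty is that the Design section assigns baseline a different role.

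The miss rates are assumed, and independence is unfavourable to the plan, so the 0.71 and 0.48 should not be read as the trial's expected power. The T5 gap is probably a slip. The Mann-Whitney test is not invalid if dropout is coded per patient.

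Missing-data detail and sphericity corrections may sit in an analysis plan that is not shown, and the authors acknowledge that more robust methods are needed, with statistical consultation still to come. That softens the point. It does not change the method that the article names.

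**Conclusion.** The point holds in this form. The named end-of-study method deletes any patient with one missed assessment in 5 years, and nothing stated for the clinical outcomes offsets this. The size is uncertain because no miss rate is given: under independent misses of 1% to 10% per visit, between 192 and 74 of 212 patients would be complete, and more if misses cluster. Whether completers would differ between arms is plausible but cannot be shown from the documents.

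The roles of baseline and of the confounders in the ANOVA need reconciling with the stated adjustment rules. The T5 gap is a plain inconsistency and small. For dropout the stated variable type is wrong: per patient it is binary with a time, and per arm it is a single count. The practical loss is that timing is ignored and no adjustment is planned for non-random groups. The sample size itself is not in error.

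**What to change.** 1. **BPDSI.** Replace the Repeated Measures ANOVA with one likelihood-based mixed model for repeated measures. Outcomes are T1 to T10 including T5. Terms are the baseline value as covariate, group, visit, group by visit, and the confounders identified under the article's own comparability rule, named in the model statement. Include every patient with at least one post-baseline value, and report the group effect at each visit as a contrast. Add a sensitivity analysis in which missing values are allowed to be not at random, for example by delta adjustment. SPSS 25 MIXED fits the main model.
2. **Self-harm and suicidality.** Use the corresponding repeated-measures model for counts or events, since the inventory records incidents over six months.
3. **Visit-wise regressions.** If they are kept, add T5 for the two primary outcomes.
4. **Dropout.** Define it per patient. Analyse time to dropout (Kaplan-Meier, and Cox with the same baseline confounders). The article does not state that dropout dates are kept, but it does record treatment duration, from which the time should be derivable. If it is not, analyse dropout as a binary outcome with the same adjustment.

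The cost is a change of analysis wording and slightly more programming, with the same data and no extra visits. The mixed model relies on a missing-at-random assumption, which is why the sensitivity analysis belongs with it.

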#### Mediation analysis

Mediation analysis will occur through regression models, path analyses and the Sobel test. For each of the outcomes, three mediation analyses will be performed, with independent variable being the group assignment, In Model 1, the mediator will be reflective functioning, in Model 2, the defense style and in Model 3, the personality organization.

Mediation analysis will occur at T_2_, T_4_, T_6_, T_8_, T_10_ Moderation

In the multiple linear regression models described in the Evaluation of Effect, in the predictor variables, an interaction term between group assignment and age will be inserted as well.

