## Aims and hypotheses

The primary aim of this study was to evaluate whether our specialized stepped care service for BPD patients, namely, the STP-BPD would produce better outcomes for treated patients than would the standard TAU service over a longitudinal 2-year follow-up evaluation at four different time points after participant enrollment. The primary outcomes of this study address the severity of BPD manifestations as well as the symptoms of self-harm and suicidality. Furthermore, we conduct an evaluation of the costs of health care services, as well as an evaluation from a societal perspective. A crucial challenge for BPD-specific health care services would be to improve the general psychopathology; the interpersonal, psychosocial and occupational functions; and the quality of life of patients. These domains are addressed by our study’s secondary outcomes.

Additionally, we will examine the mediating effects of reflective functioning and various aspects related to personality organization, such as defense mechanisms. More specifically, we hypothesize that improvements in reflective functioning during the initial phase of treatment will predict reductions in BPD symptoms and self-injurious behavior at later stages. Age will be treated as a moderator variable in line with evidence regarding the course of the disorder, the symptoms of which, tend to decline with age (49).

In addition to the abovementioned main objectives, this study aims to translate, adapt, and analyze the psychometric properties of the instruments employed in the present research among the Greek population, as some of them have not yet been rigorously evaluated. This investigation is currently in progress for most instruments, apart from those whose Greek versions have already shown satisfactory psychometric properties. Our hypotheses are as follows: 1) Participants receiving specialized stepped care services will exhibit greater clinical improvement, and specialized stepped care services will prove to be more cost-effective than TAU services. 2) Compared with participants receiving standard TAU, those receiving specialized service will exhibit greater functional improvement as well as enhanced QOL. 3) The differences discerned in the outcome variables between the two groups are expected to be mediated by differences in reflective functioning, defense style and personality organization.

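### The Sobel test planned for hypothesis 3 is conservative: at 212 patients it costs from near 0 to about 20 points of power, depending on path sizes the protocol does not state

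*Protocol article*

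**What the plan says.** Hypothesis 3, under Aims and hypotheses, reads: "The differences discerned in the outcome variables between the two groups are expected to be mediated by differences in reflective functioning, defense style". The third mediator it names is personality organization. Under Mediation analysis the method is given in one sentence: "Mediation analysis will occur through regression models, path analyses and the Sobel test". The same section adds "For each of the outcomes, three mediation analyses will be performed, with independent variable being the group assignment", with one mediator per model, at T2, T4, T6, T8 and T10. No resampling interval, product-distribution interval or joint-significance rule is named. The general rule for tests is "All significance tests will be two-tailed, with a 5% significance level and 95% confidence interval".

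The sample size of 212 (106 per group, power 0.90) was set for the group difference in outcome: "The power calculation was based on a moderate effect size (Cohen’ s d= 0.45) due to the naturalistic character of the study". No path coefficient, and no power figure, is given for mediation.

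Under Limitations and challenges, the article says that a statistician will be consulted later and concedes in general terms that more modern, robust methods are needed. It does not name the mediation test there.

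**The concern.** The null hypothesis is that the indirect effect, the product of path a (group to mediator) and path b (mediator to outcome), is zero. The Sobel test divides the estimated product by its approximate standard error and compares the ratio with ±1.96. That reference is adequate when at least one path is estimated far from zero. When both are modest, the product has a skewed, peaked distribution and the ratio is too rarely extreme.

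The stake is a missed mechanism. The article also relies on the mediation pathway as an argument for the study's internal validity. A non-significant Sobel result could be read as evidence against that pathway when an interval suited to a product, from the same two regressions, would exclude zero.

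**Working it through.** **1. Reproduce the stated sample size.** Inputs from Sample size: d = 0.45, power 0.90, two-sided 5%. The normal formula gives n per arm = 2 × (1.960 + 1.282)² / 0.45² = 103.8, so 104. The two-sample t test gives 105 per arm (210 in total), and power at 106 per arm is 0.903. The planned 212 is confirmed, but for the group comparison only.

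**2. Why the Sobel ratio is too small.** Write A and B for the z-values of the two paths. The Sobel statistic is AB / √(A² + B²). If A = B = 2.5, each path is significant on its own, yet Sobel gives 2.5 / √2 = 1.77, below 1.96. With equal paths, each z-value must exceed 1.96 × √2 = 2.77.

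**3. Expected z-values at N = 212.** Let a be the standardised group difference in the mediator, and b the partial correlation of mediator and outcome given group. Then A = a × √(212/4) and B = b / √(1 − b²) × √212.
- a = 0.45, b = 0.20: A = 3.28, B = 2.97, Sobel ratio = 2.20.
- a = 0.45, b = 0.40: A = 3.28, B = 6.35, Sobel ratio = 2.91.

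As B grows, the ratio approaches A and the penalty disappears.

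**4. Simulated power at N = 212.** One mediator, equal groups, normal errors, complete data, no covariates, no direct effect. There were 8,000 replicates per cell, and the first 4,000 were used for the product-distribution interval. The values of a are borrowed from the outcome effect sizes in Sample size (0.45, and the cited 0.31 and 0.56). The values of b are assumptions.

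| a | b | Sobel % | Joint significance % | Product interval % | Sobel loss v product interval (points) |
|---|---|---|---|---|---|
| 0.31 | 0.14 | 13.2 | 32.7 | 30.6 | 17 |
| 0.31 | 0.20 | 30.2 | 51.5 | 49.4 | 19 |
| 0.31 | 0.30 | 50.4 | 61.0 | 59.3 | 9 |
| 0.31 | 0.50 | 59.7 | 61.5 | 60.5 | 1 |
| 0.45 | 0.14 | 28.5 | 47.8 | 48.3 | 20 |
| 0.45 | 0.20 | 57.7 | 75.7 | 75.3 | 18 |
| 0.45 | 0.25 | 75.3 | 86.7 | 87.6 | 12 |
| 0.45 | 0.30 | 83.9 | 89.9 | 91.1 | 7 |
| 0.45 | 0.40 | 88.5 | 90.4 | 91.4 | 3 |
| 0.45 | 0.50 | 89.2 | 90.1 | 89.8 | 1 |
| 0.56 | 0.20 | 69.4 | 81.2 | 79.3 | 10 |
| 0.56 | 0.30 | 95.4 | 97.7 | 98.0 | 3 |

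The simulation standard error of a single percentage is at most √(0.25/4000) = 0.8 points.

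A separate run with the percentile bootstrap agrees. Sobel against bootstrap was 25% v 46% at 0.30/0.20 and 54% v 72% at 0.45/0.20. The loss was about 7 points at 0.45/0.30 and 3 at 0.45/0.40.

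**5. Upper bound.** Over a grid of path z-values with 200,000 draws, the largest loss against joint significance was 23.8 points (31.7% v 55.5%), at z-values of 2.5 and 2.75. Losses of 18 to 20 points are therefore close to the worst case.

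**6. Rejection under the null at N = 212.**
- Both paths zero: Sobel about 0.0%, product interval 0.1%.
- a = 0.45, b = 0: Sobel 1.6% (1.8% in the bootstrap run), product interval 4.4%, joint significance 4.6%.
- a = 0, b = 0.50: Sobel 4.4%, product interval 4.6%.

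**7. Fewer patients.** At N = 158 (used here only as an assumed attrition level) and a = 0.45, Sobel against the product interval is 35.0% v 57.3% at b = 0.20, 65.9% v 78.7% at b = 0.30, and 78.7% v 82.2% at b = 0.50.

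**The case against.** The best defence has four parts.

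- **The error is on the safe side.** A conservative test does not inflate false positives, hypothesis 3 is mechanistic, and the primary comparison is untouched. This stands, and it limits the importance of the point.
- **The loss may be small.** The article gives no path sizes. Mediator and outcome overlap in content: the IPO covers identity pathology and the BPDSI has an identity area. A strong b path is therefore possible, and the loss would then be a few points at most. In the other direction, if the total effect and the mediator shift are both 0.45, b = 0.20 already means that one of three proposed mediators carries 0.45 × 0.20 / 0.45 = 20% of the effect. The reported RFQ internal consistency (.77 and .65 in the clinical sample) would also weaken the observed paths. The document does not settle which case applies.
- **The plan names other tools.** Regression and path analysis give a test of each path, and joint significance recovers nearly all the lost power. But the article states no decision rule built on those tests, and Sobel is the only named test of the product. The general concession under Limitations and challenges replaces nothing.
- **The simulation is idealised.** The planned models carry covariates, data will be incomplete, and one primary outcome consists of self-harm and suicide incidents. This stands: the figures show the order of the loss and do not forecast it.

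A reader might infer that 20 points is a fixed cost of the plan, or that a negative Sobel result is likely. Neither is supported. The loss depends on unstated path sizes, and Sobel power is 58% at 0.45/0.20 and 84% at 0.45/0.30. Where the group-to-mediator path limits power, as at 0.31/0.50, the two methods perform almost alike (60% v 61%).

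**Conclusion.** The point holds as a cheap improvement to the analysis of hypothesis 3. The named test is conservative because its normal reference does not suit a product of two coefficients: about 2% rejection at N = 212 with a = 0.45 and b = 0. Against a percentile-bootstrap or product-distribution interval, the loss of power at 212 patients ranges from near 0 to about 20 points:
- about 18 to 20 points with b near 0.20 and a from 0.30 to 0.45;
- about 7 points at 0.45/0.30;
- 3 or less from 0.45/0.40.

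These figures rest on assumed path sizes, normal errors, complete data and no covariates. It would be wrong to say that Sobel falls well short of 5% under every null, since it reaches 4.4% at a = 0, b = 0.50. It would also be wrong to say that the alternative is always calibrated, since both methods are far below 5% when both paths are zero.

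**What to change.** Under Mediation analysis, replace the Sobel test with a 95% percentile-bootstrap (or product-distribution) confidence interval for the indirect effect. Take it from the same regressions with the planned covariates included, and state that the mediation conclusion rests on whether the interval excludes zero.

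This is one sentence of text. It needs no new data and no change in sample size. The product-distribution version needs only the two coefficients and their standard errors; the bootstrap needs the models refitted on resampled patients. The downside is a little extra computing.

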We designed this study to evaluate the effectiveness and economic aspects (cost-effectiveness and cost-utility) of the STP-BPD in everyday clinical practice, adhering to the call for *‘real-world’* clinical trials (55, 56). Therefore, we will use minimal exclusion criteria without altering clinical decision-making, health care, or treatment. Patients will be followed for 2 years for primary and secondary outcomes, and for additional 3 years for primary outcomes only. Assessment of the clinical and psychosocial outcome variables will be performed at baseline (T_0_), prior to patient allocation, and every 6 months until the end of the 2^nd^ year of follow-up (T_1_, T_2_, T_3_, and τ_4_). At baseline (T0) and then every year thereafter (τ2 and τ4), the mediators that affect the link between the type of health care service and the major clinical and psychosocial outcomes will be examined. For long-term evaluation, primary outcome variables will also be assessed at T_5_ (2 years and 6 months), T_6_ (3 years), T_7_ (3 years and 6 months), T_8_ (4 years), T_9_ (4 years and 6 months) and T_10_ (5 years). Patient flow, screening and assessments are displayed schematically in **Figure 1**.

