**Figure 1 f1:**
[figure not shown]
Flowchart of the study design.

Primary outcomes will be (i) the severity of BPD symptoms and (ii) the severity of self-harm and suicidality. Secondary outcomes will be: (i) psychopathological symptom severity, (ii) quality of life, (iii) quality and intensity of interpersonal relations, (iv) functioning and (v) disability.

Mediator variables will be: (i) reflective functioning, (ii) defense style and (iii) personality organization. In other words, better primary and secondary outcomes for the intervention group as opposed to TAU group are expected to be discerned due to differences in reflective functioning, defense style and personality organization. As the design does not include random allocation of participants in the two arms, baseline measurements of the outcome variables will be considered as confounders for the ensuing measurements. Moreover, the two groups will be compared in terms of the following variables: sex, family status, education status, number of children, profession, living arrangement, physical illness, medication for BPD and prior hospitalize physical illness, medication for BPD and prior hospitalization. Those variables with a statistically significant difference between the two groups, will be considered confounder variables in the design and will be taken into consideration as such in ensuing evaluation points. Moreover, information about the treatment delivered in the two groups will be recorded; namely, duration of treatment, type and number of sessions attended. These will be included as confounder variables in the design.

The Ethics Committees of Eginition Hospital, Medical School of the National and Kapodistrian University of Athens (No. 404/05-07-2021), Attikon Hospital (No. 443 25/08/2021), and Sismanogleion General Hospital (27703/10-12-2021) approved the research protocol. The Clinical Trials.gov website has registered the trial under the ID NCT06392139 (Protocol ID No. 404/06-07-202).

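### The mediation models make no provision for the baseline (T0) value of the mediator, so with non-random groups a pre-existing difference in the mediator can be reported as mediation

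*Protocol article*

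**What the plan says.** **The models.** Under Mediation analysis the article gives the method: "Mediation analysis will occur through regression models, path analyses and the Sobel test". It sets up three models per outcome, "with independent variable being the group assignment, In Model 1, the mediator will be reflective functioning, in Model 2, the defense style", and personality organization in Model 3. It lists no covariates and does not say whether the mediator enters as a level or as a change.

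**When the mediators are measured.** The Design section schedules them: "At baseline (T0) and then every year thereafter (τ2 and τ4), the mediators that affect the link" will be examined. Table 1 agrees, with RFQ, DSQ-40 and IPO-GR at T0, T2 and T4.

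**What is compared or adjusted at baseline.** Four places address this:
- Design (text after Figure 1): "As the design does not include random allocation of participants in the two arms, baseline measurements of the outcome variables will be considered as confounders", plus a named list of demographic and clinical variables.
- Assessing the comparability of the two groups: "the two groups will be compared for potential differences in all primary and secondary outcome variables", then socio-demographics, physical illness and medication. Socio-demographic and other variables that differ significantly are carried into later analyses.
- Evaluation of effect: the baseline of the outcome, treatment duration, number of sessions and the confounders found at baseline.
- Limitations and challenges: baseline outcomes, socio-demographic and medication variables.

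None of the four names a mediator.

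**The hypothesis.** Aims and hypotheses frames it as change: "we hypothesize that improvements in reflective functioning during the initial phase of treatment will predict reductions in BPD symptoms". The Design section (differences on the mediators) and Limitations and challenges (better mediator scores explaining better outcomes) read as levels.

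**The concern.** Patients reach the two arms through different centres and referral routes, so the groups may differ in mentalizing, defenses or personality organization before treatment. If the T2 or T4 mediator is regressed on group alone, the group coefficient mixes that prior difference with any change due to the service. The null hypothesis tested is then that the groups have the same mediator level. The null of interest is that the service does not change the mediator.

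Adjusting for the T0 outcome does not cure this, because the T0 outcome is only partly correlated with the T0 mediator. Hypothesis 3 is at stake. So is an argument in Limitations and challenges, where the specified pathway is offered as strengthening internal validity. A baseline gap read as mediation would feed directly into that causal claim.

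**Working it through.** **Inputs from the protocol.** 106 per group; two-sided 5% tests; Sobel test; mediators measured at T0, T2 and T4; non-random groups. The plan gives no figure for the mediation analysis. Its sample size reproduces (d = 0.45, power 0.90: 105 per group by t-test against 106 stated, power 0.903 at 106) and is used here only to set N.

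**Inputs assumed.** The T0 mediator gap *d* (in SD), the T0-T2 mediator correlation *r*, and the mediator-outcome links. None is in the document.

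**Step 1: the group-to-mediator path.** Let *e* be the service effect on the mediator. Without the T0 mediator, a = r·d + e; with it, a = e. For e = 0, d = 0.3 and r = 0.7, the unadjusted path is 0.7 × 0.3 = 0.21 although nothing changed.

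**Step 2: the indirect effect.** Assume Y0 = 0.4·M0 + noise and Y2 = 0.6·Y0 + 0.3·M2 + noise (residual SD 0.7), with no direct group effect.
- No covariates: b = 0.3 + 0.6 × (0.4 × 0.7) = 0.468, so a·b = 0.21 × 0.468 = 0.098 (simulated 0.097).
- T0 outcome in both equations: a = 0.21 − (0.4 × 0.7) × (0.4 × 0.3) = 0.176 and b = 0.3, so a·b = 0.053 (simulated 0.053).
- T0 mediator in both equations: a = 0, so a·b = 0.

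**Step 3: false Sobel significance** under that model, 3,000 simulated trials per row.

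| T0 gap (SD) | r | No covariates | T0 outcome in both | T0 mediator in both | T0 mediator and T0 outcome in both |
|---|---|---|---|---|---|
| 0 | 0.5 | 3.8% | 3.4% | 2.3% | 3.6% |
| 0 | 0.7 | 4.9% | 4.2% | 2.2% | 3.1% |
| 0.2 | 0.5 | 10.4% | 8.2% | 2.8% | 3.8% |
| 0.2 | 0.7 | 15.9% | 11.7% | 1.6% | 2.5% |
| 0.3 | 0.5 | 16.3% | 12.2% | 2.4% | 3.3% |
| 0.3 | 0.7 | 30.1% | 21.6% | 1.6% | 2.7% |
| 0.5 | 0.5 | 41.5% | 30.9% | 2.5% | 3.3% |
| 0.5 | 0.7 | 69.0% | 54.9% | 1.6% | 2.7% |

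**Step 4: a second set of assumptions.** r = 0.75, Y0 = 0.5·M0 + noise, Y2 = 0.45·Y0 + 0.25·M2 + noise. The lower figure has the T0 outcome in both equations, the higher one in the outcome equation only.
- Gaps of 0.2, 0.3 and 0.4 SD: about 9-13%, 17-26% and 31-47%.
- T0 mediator in both equations: 1-2%.
- No gap: about 2%. Gap of 0.1 SD: about 5%.
- Sensitivity at 0.3 SD: with outcome residual SD 0.7, 0.8 and 1.0, the T0 outcome in the outcome equation only gives 30%, 25% and 18%; in both equations it gives 21%, 17% and 11%.

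**Step 5: would a baseline significance screen catch the gap?** With 106 per group, a t-test detects gaps of 0.2, 0.3 and 0.5 SD with power 31%, 58% and 95%. A screen would therefore miss a 0.3 SD gap in about 42% of trials (100 − 58) and a 0.2 SD gap in about 69% (100 − 31).

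**Step 6: power with balanced groups and a true mediator change of 0.3 SD.** One run gave 44% without and 58% with the T0 mediator (50% with only the T0 outcome in both equations). At outcome residual SD 1.0 the figures were 35%, 39% and 40% respectively, so the T0 mediator then gains nothing over the T0 outcome.

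**The case against.** The strongest objection is that a reader might infer that the plan commits to the unadjusted post-treatment level. The article does not say so. The mediation section is short and lists no covariates. The aims speak of improvement, and the T0 measurements are what a change analysis needs. If the mediator entered as T2 minus T0, the Sobel test would reject in only 0.3% to 2.3% of trials at gaps of 0.2 to 0.4 SD under the Step 4 model. A condensed article may also leave covariates to a fuller plan. The ambiguity stands. But the article states its baseline-adjustment rule four times, always for outcomes and background variables only, and its own gloss on mediation in two places is about levels. A change score would also not fully remove the gap: its group path is (r − 1)·d, or −0.25 × 0.4 = −0.1 for r = 0.75 and d = 0.4.

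The comparability section's clause on other significantly different variables is open-ended and reaches all later analyses. It helps only variables that are tested, and the mediators are not among those named. Step 5 shows that a significance filter would be unreliable even if they were.

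A reader might also infer that false mediation will occur. The documents report no baseline gap, and Limitations and challenges gives a reason to expect similar severity, since both arms are hospital-affiliated services. With no gap there is no inflation. Finally, mediation is hypothesis 3 and not the primary comparison, and the article concedes that internal validity is open to question and that a statistician is still to be consulted.

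**Conclusion.** The point holds as a gap in the stated plan. The T0 mediator is collected but appears in no mediation model, covariate list or baseline comparison, in a design where the groups may differ from the start. Followed as written, the analysis can report a prior difference as mediation. It also does not match the improvement hypothesis in the aims.

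The size is conditional: about 9% to 47% false significance for T0 gaps of 0.2 to 0.4 SD under the Step 4 assumptions, against 1% to 2% with T0 adjustment. Step 3, with different assumptions, shows the same pattern. Gap, stability, slopes and residual variances are all assumed. The low adjusted rates also suppose that the measured T0 score carries the whole prior difference. The Mediators section gives RFQ internal consistencies of .77 and .65 in the clinical sample, so some residual gap could remain.

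The documents do not support saying that mediation will be falsely declared, that the plan expressly excludes T0, or that omitting T0 always costs power. The primary outcome comparison is unaffected.

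**What to change.** Under Mediation analysis, state that every mediation model includes the T0 value of the mediator and the T0 value of the outcome in both the mediator equation and the outcome equation, whether or not they differ significantly at baseline. The group-to-mediator path then compares groups at equal baseline mediator scores, which fits the improvement hypothesis.

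Under Assessing the comparability of the two groups, add RFQ, DSQ-40 and IPO at T0 to the baseline comparison.

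The cost is a sentence in each section and one or two extra covariates per equation. All the values are already scheduled in Table 1, so no new data are needed.
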